### Statistical analysis

#### Sample size

Cognitive impairment, anxiety, and depression are reported in about 20%-30% of patients from populations similar to ours [5, 8, 12, 14] while the prevalence of frailty is reported to be as high as up to 50% [21, 27]. Hence, to estimate the required sample size, we assumed an expected prevalence of 25%. Accordingly, the sample size required to estimate this prevalence with a 95% level of confidence and a margin of error of 5% was 288 subjects. Making a conservative choice, we assumed a sample size equal to 300 subjects. This number allows to estimate, with the same accuracy, prevalence values up to 50% with a 90% level of confidence.

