**Methods and design:**

This study protocol of a prospective multi-center clinical trial, will be conducted at two hospitals of the Istituti Clinici Scientifici Maugeri IRCCS group, from July 2020 until December 2022. CHF and COPD older patients (age ≥65) will undergo a multidisciplinary assessment at admission, discharge and at 6 months follow-up, from an inpatient rehabilitation program: disease-related clinical characteristics, functional variables, cognitive screening, treatment adherence, anxiety, depression, QoL and frailty. The estimated sample size will consist of 300 patients

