In this vein, the current study aims to bridge this gap. In particular, this paper presents the study protocol of a prospective clinical trial that evaluates and compares socio-demographic, clinical and functional characteristics, cognitive impairment, treatment adherence, anxiety, depression, perceived QoL, and frailty in a sample of older (age ≥65) CHF and/or COPD inpatients, at admission, discharge, and after 6 months from a cardiac or pulmonary rehabilitation program. Another aim is to verify the appropriateness of a frailty screening tool, the Clinical Frailty Scale (CFS), in cardiorespiratory rehabilitation setting, by comparing it with the gold standard, Frailty Index.

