## Discussion

The primary endpoint of the study is to define a multidimensional profile of the two clinical samples to better plan the rehabilitative intervention. The assessment of clinical and functional status, cognitive impairment, treatment adherence, psychosocial characteristics, and frailty could provide more specific and useful information about the main features to be considered in the evaluation and treatment of older patients suffering from CHF and COPD undergoing a rehabilitative pathway.

The secondary endpoint is to define the usability of the CFS with chronic patients in an interdisciplinary rehabilitation setting to routinely screen frailty. We expected that this tool results reliable in comparison to the gold standard (FI).

Furthermore, we expected to use the patients’ multidimensional profiles in order to tailor and improve the rehabilitative intervention over time and to implement the CFS scale to monitor the rehabilitative process.

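### The ±5-point margin behind the 288/300 sample size holds for all patients pooled, while the primary endpoint is a profile of two samples, CHF and COPD, which 300 patients cannot both serve at that precision

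*Protocol article*

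**What the plan says.** In the Sample size section the planning value is a single prevalence: "to estimate the required sample size, we assumed an expected prevalence of 25" per cent. From it, "the sample size required to estimate this prevalence with a 95% level of confidence and a margin of error of 5% was 288 subjects". The next step is "Making a conservative choice, we assumed a sample size equal to 300 subjects", followed by a second precision statement: "This number allows to estimate, with the same accuracy, prevalence values up to 50% with a 90% level of confidence". The Abstract (Methods and design) shows that 300 is the total for the study and not a number per disease: "The estimated sample size will consist of 300 patients".

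The Discussion sets the target of estimation: "The primary endpoint of the study is to define a multidimensional profile of the two clinical samples". The rest of the article treats these as separate groups. Participants defines CHF and COPD by different criteria and recruits from a cardiac and a pulmonary department. Clinical evaluation lists different disease measures for each. The Introduction admits patients with either or both conditions: "CHF and/or COPD inpatients, at admission, discharge, and after 6 months from a cardiac or pulmonary rehabilitation program".

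The article gives no CHF:COPD split, no target number per disease and no precision per disease.

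**The concern.** A margin of error belongs to the group whose prevalence is being estimated. The calculation treats that group as all 300 patients. The primary endpoint calls for prevalences of cognitive impairment, anxiety, depression and frailty within CHF and within COPD, and each of these rests on a fraction of the 300.

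The precision offered to justify the sample size is therefore not the precision with which the primary endpoint will be estimated. A reader would naturally attach ±5 points to the disease-specific prevalences, whose intervals will be wider, and widest in whichever group recruits fewer patients.

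**Working it through.** **Inputs from the article (Sample size):** p = 0.25; margin d = 0.05; 95% confidence; total N = 300; second statement at p = 0.50 with 90% confidence; cited range of 20%–30% for cognitive impairment, anxiety and depression, and up to 50% for frailty. **Assumption:** the split between diseases, which the article does not give and which is varied below.

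**1. Reproducing the stated figures (pooled sample).** Formula: n = z²·p(1−p)/d².

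- 95%, p = 0.25: 1.960² × 0.1875 / 0.0025 = 288.1. The stated 288 is reproduced.
- 90%, p = 0.50: 1.645² × 0.25 / 0.0025 = 270.6, below 300. The second statement is reproduced.
- With n = 300 the half-width z·√(p(1−p)/n) is ±4.9 points (25%, 95%) and ±4.75 points (50%, 90%).

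**2. What ±5 points in each disease would require.**

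- 25%, 95%: about 288 per disease, so 2 × 288 = 576 patients if the groups do not overlap.
- 50%, 90%: 271 per disease, so 2 × 271 = 542.
- For both groups to reach 288 within 300 patients, the overlap must be at least 288 + 288 − 300 = 276, that is 92% of the study with both diseases.
- At the favourable end of the article's range, 20%, the requirement is still 245.9 per disease, or about 492 in total. The conclusion does not depend on the choice of 25%.

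**3. Half-widths per disease with N = 300, no patient counted twice (95%, p = 0.25).**

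| Assumed split | Larger group | Smaller group |
|---|---|---|
| 150/150 | ±6.9 | ±6.9 |
| 180/120 | ±6.3 | ±7.7 |
| 200/100 | ±6.0 | ±8.5 |
| 240/60 | ±5.5 | ±11.0 |

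For 150/150 the line is 1.960 × √(0.1875/150) = 0.0693.

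**4. Other prevalences at 150 per disease.**

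- 20%: ±6.4; 30%: ±7.3 (95%).
- 50%: 1.960 × √(0.25/150) = ±8.0 (95%), and 1.645 × √(0.25/150) = ±6.7 (90%). The second precision statement is not met per disease either.
- Put the other way, ±5 points at 150 per disease corresponds to about 84% confidence at 25% and about 78% at 50%.

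**5. The extreme split.** Without overlap, one disease reaches ±5 points at 25% only with about 288 of the 300 patients. That leaves 12 in the other, at ±24.5 points.

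**The case against.** The strongest reply is that no stated number is wrong. Both precision statements reproduce for the pooled sample, and the article never promises ±5 points per disease. That stands: this is a mismatch between the quantity sized and the quantity named as primary, not an error of calculation. The study is also descriptive. Wider intervals bias no estimate, and intervals computed per disease from the data would show their true width. This limits the harm, but it does not make the justification apply to the primary endpoint.

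A further reply is that the call for estimates per disease rests on one sentence in the Discussion. That sentence defines the primary endpoint, however, and the separate case definitions, departments and disease measures agree with it.

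Four stronger readings are tempting, and the article does not support them.

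- A reader might infer that a CHF-versus-COPD comparison is planned and underpowered. The comparison named in the Introduction is over time within one sample, and the Statistical analysis section names paired tests, correlations and a general linear model, with no test between diseases.
- A reader might infer that calling 300 conservative is false, because 30% prevalence would need 323 patients. In context the word describes only the step from 288 up to 300. At 30% the pooled margin is ±5.2 points, a small excess over 5.
- A reader might infer that the weaker precision at 50% is concealed. The 90% confidence level is stated openly.
- A reader might infer that patients with both diseases have no defined place. Recruitment through two departments offers a natural basis for assignment, and the rule may sit in the full protocol or analysis plan, which are not shown.

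**Conclusion.** The point holds as a mismatch of estimation target. The ±5-point margin is correct for 300 patients pooled and does not carry over to the two samples of the primary endpoint.

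The direction is firm: at any prevalence in the article's cited range, 300 patients in total cannot give ±5 points at 95% in both diseases without extensive overlap, and at the planning value of 25% the overlap needed is near-complete. The size depends on a split that is not stated. With equal groups, the half-width at 25% is √2 times the pooled one (6.9 against 4.9, about 40% wider). With 200/100 it is ±6.0 in the larger group, 20% above the stated 5 points, and ±8.5 in the smaller, 70% above it. These figures assume the normal-approximation formula that reproduces the article's own 288, and that each patient counts in one sample only.

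**What to change.** Keep N = 300 and change the Sample size section in three respects.

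1. Say that ±5 points (95% at 25% prevalence; 90% at up to 50%) applies to the pooled sample only.
2. State the anticipated split between the two departments and the expected margin in each disease. If equal groups are expected, the text would give ±6.9 points at 25% and ±8.0 at 50% (95%), or ±6.7 at 50% with 90% confidence. If 200/100 is expected, it would give ±6.0 and ±8.5 points at 25%.
3. Assign each patient to one sample by admitting department, cardiac or pulmonary, and record a flag for dual diagnosis, so that no patient counts in both. If the full protocol already holds such a rule, refer to it here.

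No extra patients and no change to recruitment are needed. The cost is a less favourable stated precision for the primary endpoint.

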#### Statistical analysis

Continuous variables will be expressed as mean ± standard deviation, while categorical variables will be expressed as a percentage.

The investigated variables, before and after intervention, will be assessed using paired sample t-tests or Wilcoxon signed-rank tests, depending on the sample distribution. Pearson correlation coefficient or Spearman rank correlation coefficient tests will be used to evaluate the associations between these variables. A general linear model will be applied to find the factors associated with clinical, functional, and frailty outcomes. Data will be analyzed using SAS/STAT statistical package, release 9.4 (SAS Institute Inc., Cary, NC, USA). The significant level will be set at p < 0.05.

## Discussion

The primary endpoint of the study is to define a multidimensional profile of the two clinical samples to better plan the rehabilitative intervention. The assessment of clinical and functional status, cognitive impairment, treatment adherence, psychosocial characteristics, and frailty could provide more specific and useful information about the main features to be considered in the evaluation and treatment of older patients suffering from CHF and COPD undergoing a rehabilitative pathway.

The secondary endpoint is to define the usability of the CFS with chronic patients in an interdisciplinary rehabilitation setting to routinely screen frailty. We expected that this tool results reliable in comparison to the gold standard (FI).

Furthermore, we expected to use the patients’ multidimensional profiles in order to tailor and improve the rehabilitative intervention over time and to implement the CFS scale to monitor the rehabilitative process.

### Strengths and limitations

A first limitation of this study concerns the estimated sample size since the COVID-19 pandemic outbreak could interfere with the recruitment of patients. A second limitation regards the assessment of treatment adherence, psychological distress and quality of life (QoL), evaluated through self-report measures. This limitation could be due to different reasons such as risk of false-positives and lack of sensitivity to change, psychometric adequacy of the assessment instrument and social desirability bias. Nevertheless, some advantages like high practicality of use, clinical and research applicability, and cost-effectiveness could be identified as positive aspects. Another strength of the study consists in the involvement of different healthcare professional figures that perform the evaluation and the intervention in a multidisciplinary way. Finally, frailty is often considered in rehabilitation settings, but its evaluation is not always performed with standardized methods and measures as in the present research protocol.

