#### Frailty evaluation

Clinical Frailty Scale (CFS) is a scale developed in Canada, which is based on clinical judgment only with a score ranging from 1 to 9: 1) Very Fit; 2) Well; 3) Managing Well; 4) Vulnerable; 5) Mildly Frail; 6) Moderately; Frail; 7) Severely frail; 8) Very severely Frail; 9) Terminally Ill [46]. This scale considers clinical data on the subject’s cognition, mobility, functional abilities, and comorbidity, which can be collected through the medical history obtained from the patient, the caregiver, and/or other healthcare providers [46].

Frailty Index (FI) is a frailty measurement tool created through a geriatric assessment study including non-institutionalized patients. The variables taken into consideration are mobility, muscle strength, comorbidities, cognitive deficits, mood, anthropometric indices, mini nutritional assessment, and social support. It is made up of 40 items and 17 additional items relating to the Social Support Scale [22, 47].

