#### Nurse

The nurse is generally the first healthcare operator who meets the patient and has contact with the family members. The nurse assessment includes, at admission and at discharge, the use of validated and sensitive scales (BI, BI-D, and Braden) to verify if the goals of the rehabilitation program have been achieved. The tasks of nurses are to identify the risk factors and intervene in them and in the particular disabilities, and to promote adherence to pharmacological and non-pharmacological therapy.

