#### Physiotherapist

The physiotherapist’s intervention aims to achieve the patient’s maximum possible recovery of functional capacity and autonomy. Treatment consists in two daily sessions lasting from 30 to 45 minutes of cycle-ergometer and/or treadmill, leg ergometer and breathing exercises. The initial assessment phase consisting of SPPB, TUG, and 6MWT allows the selection of the most appropriate treatment related to the patient’s functional needs, while the final assessment permits to verify the results achieved and to plan an appropriate maintenance program.

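### Discharge CFS, and to a lesser degree BI and Braden, are rated by the professions that deliver the programme, which leaves an unacknowledged risk of assessor bias toward improvement in the pre-post tests

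*Protocol article*

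**What the plan says.** - **Nurse** (Intervention). The nurse works on risk factors and disabilities and also assesses the patient at admission and discharge through "the use of validated and sensitive scales (BI, BI-D, and Braden) to verify if the goals of the rehabilitation program have been achieved".
- **Physiotherapist** (Intervention). The section covers the treatment sessions and the initial SPPB, TUG and 6MWT, "while the final assessment permits to verify the results achieved and to plan an appropriate maintenance program".
- **Frailty evaluation** (Materials). The CFS is a scale "which is based on clinical judgment only with a score ranging from 1 to 9", running from very fit to terminally ill, so a lower score is better.
- **Data collection.** At baseline (T0), CFS and Frailty Index (FI) are rated jointly by three of the listed professional groups and nurses. At discharge (T1), eleven instruments are repeated, among them BI, Braden, TUG, 6MWT and CFS. The T1 paragraph names no raters. In the text, the FI is listed at T0 only.
- **Statistical analysis.** Values before and after the intervention are compared by paired t-test or Wilcoxon signed-rank test at p < 0.05. No control group is described.
- **Abstract, Discussion.** Improvement after the programme, and its maintenance, are the expected results.
- **Strengths and limitations.** The "involvement of different healthcare professional figures that perform the evaluation and the intervention in a multidisciplinary way" is a strength. The only measurement limitation given concerns self-report measures, with social desirability among the reasons.

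**The concern.** A rater who has helped to treat a patient, and who is asked at discharge whether the programme worked, may rate generously without intending to. The risk grows with the amount of judgment in the scale and with knowledge of the earlier score. In a controlled trial with the same raters in both arms, part of such leniency could cancel. Here it goes straight into the within-patient difference, and no analysis of these data can separate it from true recovery.

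What is at stake is the claim that frailty and function improve between admission and discharge. The Discussion also foresees using the CFS to monitor the rehabilitative process, so the meaning of a CFS change matters beyond this study. The protocol recognises response bias when patients rate themselves, but says nothing of the parallel risk when staff rate the patients they treat.

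**Working it through.** **1. The plan's own figure.** The sample size is a precision calculation: n = z² p(1 − p)/d² = 1.96² × 0.25 × 0.75 / 0.05² = 288.1, against the stated 288, raised to 300. It reproduces. It concerns prevalence, so assessor bias in a change score does not touch it.

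**2. How far each discharge measure is exposed.**

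| Measure | Basis of score | Exposure |
|---|---|---|
| CFS | clinical judgment only | strongest |
| BI, Braden | staff-scored items with some judgment | weaker |
| TUG, 6MWT | seconds, metres | small, though encouragement can matter |
| EQ-5D-5L, EQ VAS | patient's own report | not a staff rating |

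**3. How sensitive the paired test is to a systematic shift.** The documents give neither a size for rater leniency nor an SD of change, so both are assumptions here. Let the true change be zero, and let b be the systematic favourable shift in SDs of change. The two-sided 5% rejection probability, by normal approximation, is

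Φ(b√N − 1.96) + Φ(−b√N − 1.96).

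| b | N = 300 | N = 150 (assumed single disease group) |
|---|---|---|
| 0 | 5% | 5% |
| 0.05 | 14% | 9% |
| 0.10 | 41% | 23% |
| 0.15 | 74% | 45% |
| 0.20 | 93% | 69% |

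For N = 300 and b = 0.10: b√N = 0.10 × 17.32 = 1.73, and Φ(1.73 − 1.96) = 0.41; the second term is negligible.

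In CFS units, suppose one patient in 20 is rated one level better without true change, a mean shift of 0.05. If the SD of change is 0.5, then b = 0.10 and the probability is 41%. If the SD is 1.0, then b = 0.05 and it is 14%.

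**4. The same in patients.** If every non-zero CFS difference is one level, all ranks are equal and the Wilcoxon test reduces to the sign test.

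- No other rating changes: 6 better and 0 worse gives p = 2 × 0.5⁶ = 0.031.
- With ordinary rating noise, 61 of 300 patients (20%) changing: 39 better and 22 worse gives p = 2 × P(Bin(61, 0.5) ≤ 22) = 0.040. With 38 and 22 it is 0.052. The net excess needed is 39 − 22 = 17 patients, or 17/300 = 5.7%.

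The second case is the more realistic one for a judgment scale. Both show how sensitive the test is; neither estimates bias in this study.

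**The case against.** The strongest reply has four parts.

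- **The text names professions, not persons.** It does not say that the same individual rates a patient at T0 and T1, or that T0 scores are in view at T1. The discharge CFS rater is inferred from the baseline paragraph, and a condensed article may leave such detail to the full protocol. This stands. It limits the point to a risk, but does not remove it: the Nurse section gives treatment and discharge rating to one profession and describes the rating as a check on programme goals.
- **The strengths sentence praises multidisciplinary work, not non-independent rating.** This stands too, so the sentence need not be withdrawn. What is lacking beside it is the matching limitation.
- **Neither named endpoint is affected.** The primary endpoint is a descriptive profile. The secondary sets CFS against FI, and the text lists the FI only at baseline. This is correct; the point reaches only the pre-post comparisons.
- **An outside rater has costs of its own.** One rater at discharge in place of the interdisciplinary baseline rating would measure the two time points differently and add between-rater variance to the difference. It might also need staff who are not described. This stands, and the remedy should not require it.

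A reader might infer that the observed improvement is in fact biased, or that a handful of generous ratings would decide the CFS test. The documents support neither. They contain no evidence of leniency and no size for it. The six-patient case needs the other 294 ratings to be identical at both times; with modest noise a net 17 patients are needed. Nor does the concern extend evenly to all discharge measures.

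**Conclusion.** The point holds as an unacknowledged risk of assessor bias, directed toward apparent improvement, in the admission-to-discharge change of staff-rated scales: most for CFS, less for BI and Braden. It rests on the stated roles of the professions, on the CFS being judgment-only, on the uncontrolled paired test, and on the inference that the discharge CFS is rated by the same team as at baseline. Its size cannot be derived from the documents. The figures above show only that a modest shift (0.10 SD of change, or a net excess of about 6% of patients under the stated noise) could matter with 300 patients.

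**What to change.** 1. **Discharge scoring.** Score the T1 CFS by the same interdisciplinary procedure as at T0, with the T0 score out of sight until the T1 form is closed. Do the same for BI and Braden where the T0 scores are not needed for care. A rater less involved in that patient's treatment may be used where one is already available, but is not required.
2. **Strengths and limitations.** Keep the statement on multidisciplinarity. Add that discharge CFS, BI and Braden are rated by the professions that deliver the programme and may be biased toward improvement.
3. **Interpretation.** Read the pre-post change on these three scales alongside the timed or measured tests, TUG and 6MWT.

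The cost is minor form handling and a sentence or two of text. Hiding the T0 score reduces anchoring but does not hide that the programme is complete, so the limitation statement is needed in any case. The apparent improvement may shrink. Recruitment was planned from July 2020 to December 2022: if the scoring change comes partway, record its start date so that the two procedures can be told apart. If data collection is over, items 2 and 3 still apply.
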